### Social Media Engagement

Social media data will be collected from platforms commonly used within participants’ networks, including Facebook and Instagram. Promotores will be trained to export data from their posts (e.g., Facebook JSON exports) and share these files with the research team. For platforms that do not support direct data export, alternative approaches will be used, including participant-reported metrics or researcher access to social media groups or communication channels, as appropriate.

Engagement metrics will include impressions (i.e., number of users who view a post) and indicators of interaction such as likes, comments, and shares. In addition, the content of promotores’ posts and associated audience responses will be analyzed to characterize features of communication, including sentiment, use of personal narratives, and incorporation of scientific evidence. These measures will be used to examine how characteristics of social media content relate to engagement within promotores’ networks.

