### Social Media Engagement

Social media engagement will be quantified using platform-derived metrics, including impressions, likes, comments, and shares. Count-based outcomes will be analyzed using Poisson or negative binomial regression models, as appropriate based on dispersion characteristics. Continuous or ordinal survey outcomes will be analyzed using linear or cumulative link mixed models, depending on distributional assumptions. Repeated measures of generalized linear mixed models will be used to assess changes in engagement over time while accounting for clustering within promotores and neighborhood clusters under the stepped-wedge design.

Characteristics of social media posts and audience responses will be extracted using large-language models and multimodal analytic approaches applied to text, images, and video content. These characteristics will include sentiment, discussion of personal experience, presence of scientific evidence, and patterns of agreement or disagreement. These features will be incorporated as independent variables in regression and machine learning–based predictive models to examine their association with engagement outcomes and to identify characteristics of posts associated with higher levels of interaction within promotores’ social networks.

In addition to quantifying the volume of engagement, analyses will examine the nature of engagement by evaluating the content of audience responses to promotores’ posts. These analyses will provide insight into how different types of communication strategies influence both the extent and quality of interaction.

Implementation fidelity will be assessed by quantifying the number and characteristics of posts produced, including adherence to training principles such as inclusion of credible sources and use of narrative elements.

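### Features of audience responses are entered as predictors of engagement outcomes that include comment counts, although such features exist only once someone has commented

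*Protocol article*

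**What the plan says.** The passage is in the protocol article, Data Analysis, Social Media Engagement.

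- Source of the features: "Characteristics of social media posts and audience responses will be extracted using large-language models".
- The list: "These characteristics will include sentiment, discussion of personal experience, presence of scientific evidence, and patterns of agreement or disagreement". It is not divided into features of the post and features of the replies.
- Their role: "These features will be incorporated as independent variables in regression", and likewise in machine-learning prediction models, to study how they are associated with engagement.
- The outcome: "Social media engagement will be quantified using platform-derived metrics, including impressions, likes, comments, and shares".

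The same sentence that assigns the role gives the aim as finding which characteristics of posts go with more interaction. The next paragraph treats the content of replies as a description of the kind of engagement obtained, that is, as a result. The Outcomes section has the same mixture: interaction is measured by "indicators of interaction such as likes, comments, and shares", and posts are coded together with replies ("associated audience responses will be analyzed to characterize features of communication, including sentiment, use of personal narratives, and incorporation of scientific evidence").

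**The concern.** Whether replies agree or disagree is known only after people have replied, and a post with more replies has more chances to contain a disagreeing one. Comments therefore feed both sides of the model. A coefficient for disagreement can then look large although disagreement has no bearing on how far a post travels, and it cannot guide how a post is written, because it does not exist when the post is published.

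Two consequences follow. Posts without comments have no response features, so they must be dropped or given an arbitrary value. And if response features enter the same model as post features, the model conditions on a consequence of the outcome, which distorts the coefficients of interest. That touches a stated hypothesis: the last paragraph of the Background expects narrative-based posts to produce greater engagement.

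**Working it through.** The documents give no comment counts, no disagreement rates and no figure for this analysis, so there is nothing to reproduce. Every input below is an assumption, used to show direction and rough size.

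**1. Any disagreement as a predictor of comment count, with no true relation.** Let comments C be negative binomial with mean m and size k (variance m + m²/k), and let each comment disagree with probability q regardless of how many there are. D is the number of disagreeing comments.

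- P(D = 0) = (1 + qm/k)^(−k)
- E(C | D = 0) = (1 − q)m / (1 + qm/k)
- E(C | D > 0) = [m − E(C | D = 0) · P(D = 0)] / [1 − P(D = 0)]
- P(C = 0) = (1 + m/k)^(−k)

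Worked cell, m = 6, k = 1, q = 0.10: P(D = 0) = 1/1.6 = 0.625; E(C | D = 0) = 0.9 × 6/1.6 = 3.375; E(C | D > 0) = (6 − 3.375 × 0.625)/0.375 = 10.375. The rate ratio is 10.375/3.375 = 3.07. P(C = 0) = 1/7 = 14%. Among posts with at least one comment, the mean without disagreement is 3.375 × 0.625/(0.625 − 0.143) = 4.375, so the ratio is 10.375/4.375 = 2.37.

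The grid (ratio for all posts / for posts with at least one comment):

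| size k | mean m | no comments | q = 0.05 | q = 0.10 |
|---|---|---|---|---|
| 0.8 | 3 | 29% | 2.95 / 1.97 | 3.35 / 2.11 |
| 0.8 | 6 | 18% | 2.99 / 2.29 | 3.62 / 2.60 |
| 0.8 | 10 | 12% | 3.21 / 2.62 | 4.14 / 3.15 |
| 1 | 3 | 25% | 2.61 / 1.86 | 2.93 / 1.98 |
| 1 | 6 | 14% | 2.60 / 2.11 | 3.07 / 2.37 |
| 1 | 10 | 9% | 2.74 / 2.36 | 3.44 / 2.82 |

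The true ratio is 1 in every cell. Leaving out posts without comments reduces the artefact but does not remove it.

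**2. Other codings and other outcomes.** A null simulation used 300 posts, 400 replicates, gamma reach with dispersion 1 and negative binomial regression with robust standard errors. Mean comments were 2 to 10 and q was 0.1 to 0.5.

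- Number of disagreeing comments, predicting comments: rate ratio 1.19 to 2.29 per disagreeing comment, rejected in 100% of replicates at the 5% level.
- Any disagreement, predicting likes, when likes and comments share the post's reach: 2.19 to 7.17, rejected in 100%.
- The same when reach is not shared (q = 0.2, mean 4): about 1.0, with 3.5% rejection.
- Share of comments that disagree: 0.96 to 1.07, with 4.2% to 9.0% rejection, but undefined for the 9% to 33% of posts without comments.
- A feature of the post itself, fixed beforehand: 0.99 to 1.01, with 3.0% to 7.2% rejection.

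**3. Effect on a real post feature.** Suppose a feature such as narrative truly multiplies the comment rate by 1.5 (size 1, mean 3 to 10, q 0.05 to 0.20). In simulation, adding any disagreement to the model lowers the estimate to about 1.3 to 1.4.

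With share coding, the loss comes from dropping posts without comments. For size 1, E(C | C > 0) = 1 + m. If the mean without the feature is 3, the ratio becomes (1 + 4.5)/(1 + 3) = 1.375; if it is 10, it becomes (1 + 15)/(1 + 10) = 1.45.

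**The case against.** The strongest reply is that this is a loose antecedent in a condensed article. Sentiment, personal experience and scientific evidence can all be read off the post; only "patterns of agreement or disagreement" belongs naturally to replies. The stated aim concerns posts, and the following paragraph already examines reply content as a result. Coding is commonly left to an analysis plan, and with a share of comments the spurious association nearly vanishes.

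Much of this stands. The absence of a coding rule is not a finding. A reader might also infer that the protocol uses responses solely as predictors; the following paragraph shows that it does not. Nor does every engagement association arise mechanically: that holds strictly for comment counts with presence or number coding, while for likes, shares and impressions the link needs shared reach, which is confounding.

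What does not stand is that nothing wrong has been stated. The article says where the features come from, names a response feature among them and gives them all, without restriction, the role of predictor. Share coding, to which the article does not commit, still loses the posts without comments.

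**Conclusion.** The point holds as a flaw in a secondary analysis that should be corrected. Followed as written, the plan allows predictors that are consequences of the outcome. Under the assumed comment distributions, an indicator of any disagreement shows a comment rate ratio of about 2.6 to 4.1 with no true relation, or 1.9 to 3.2 among posts with at least one comment, and 9% to 29% of posts have no response features at all. The sizes depend on assumed comment counts, disagreement rates and coding; the direction for comment counts with presence or number coding does not.

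Attenuation of post features (1.5 to about 1.3 to 1.4) applies only if both kinds of feature enter one model, which the article neither states nor excludes. Post features modelled without response features, on all posts, are unaffected.

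A reader might go further and infer that the trial's main results are compromised, or that the protocol claims that disagreement causes engagement. Neither is supported. The primary outcome in Sample Size is survey-based decision-making among network members; the analysis of engagement over time is described without these features; and the sentence at issue speaks of association and prediction.

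**What to change.** In Data Analysis, Social Media Engagement, limit the independent variables for engagement outcomes to features of the post that are fixed when it goes out: for example narrative, scientific evidence, sentiment of the post itself, platform and network size. The baseline promotor survey already collects platform use and number of network members.

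Model response sentiment and agreement or disagreement only as outcomes, as a proportion of comments among posts with at least one comment, and report how many posts had none. This agrees with the section's own paragraph on reply content.

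The cost is a change of wording. No new data are needed, and Trial Status says that data collection is not yet complete. The downside is that response features no longer contribute to the predictive models, so apparent predictive accuracy may be lower.

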Despite this work, there remains a limited understanding of how health information circulates and is interpreted within Spanish-language social media networks. In particular, few studies have examined how inaccurate or misleading health information is encountered in these settings or how responses grounded in scientific evidence are received by community members. In addition, it remains unclear which communication approaches are most effective in promoting engagement, recall, and informed decision-making in real-world social media environments. Addressing these gaps is essential for developing effective and scalable approaches to communicating evidence-based health information within Spanish-speaking communities.

To address these gaps, we developed Dime La VerDAD (“Tell Me the Truth”: Verify, Debunk, and Disseminate), a structured, community-engaged social media training program designed to support promotores de salud in disseminating reliable, evidence-based information about respiratory virus prevention. The program is grounded in principles of health communication and is designed to build practical skills in identifying inaccurate health claims, developing clear and accessible messages, and engaging effectively with social media audiences.

This study will evaluate the implementation and effectiveness of the Dime La VerDAD program using a stepped-wedge design across community-based cohorts. Specifically, it will characterize how health information is shared and interpreted within Spanish-language social media networks, evaluate whether a structured, evidence-based communication training program improves the quality and reach of health messaging, and assess whether narrative-based approaches differ from standard informational content in influencing engagement and vaccination-related decision-making. We hypothesize that promotores will be perceived as trusted messengers and that narrative-based posts will result in greater engagement and improved decision-making in favor of recommended immunizations.

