### Data Analysis

Analyses will be conducted to characterize social media practices, evaluate engagement with the training program, and assess the effectiveness of communication strategies over time. All analyses will account for the stepped-wedge cluster design and repeated measures within participants and clusters.

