## Discussion

This study will evaluate a community-engaged social media intervention designed to support promotores de salud in disseminating evidence-based health information within Spanish-language networks. Building on prior research demonstrating the influence of message characteristics and trusted messengers on health communication, this study aims to address gaps in understanding how health information circulates within these networks and which communication strategies are most effective in promoting engagement and informed decision-making. By integrating training in science communication with real-world application in social media environments, this study will generate evidence on both communication processes and intervention effectiveness.

Several features of the study design strengthen its ability to evaluate communication strategies within real-world settings. The stepped-wedge design allows for evaluation of intervention effects while ensuring that all participating communities receive the intervention over time. The use of promotores further leverages trusted community-based relationships to support message dissemination. The integration of multiple data sources, including surveys, qualitative data, social media analytics, and area-level health data, enables a more comprehensive understanding of both communication dynamics and downstream outcomes than would be possible using a single method alone. Evaluating communication strategies within real-world social media environments also enhances the relevance and potential scalability of the findings.

At the same time, several challenges should be considered in interpreting the results. The non-randomized design may introduce potential confounders, although analytic approaches will account for clustering and time effects. Reliance on self-reported data may introduce reporting bias, and variation in social media platform use and engagement across participants may result in heterogeneous exposure to intervention content. In addition, the study is conducted within a single metropolitan area, which may limit generalizability to other settings. Measurement of community-level outcomes may also be constrained by the availability and granularity of publicly available data.

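### Post-feature models adjust for promotor only as clustering, so part of a promotor's network advantage may be credited to the features that promotor favors

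*Protocol article*

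**What the plan says.** In the protocol article, Data Analysis, Social Media Engagement, features of posts and audience responses are extracted by language models and then used as predictors: "These features will be incorporated as independent variables in regression and machine learning" based models. The stated aim is "to examine their association with engagement outcomes and to identify characteristics of posts associated with higher levels of interaction".

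Promotor is handled in two places. The general statement that opens Data Analysis reads "All analyses will account for the stepped-wedge cluster design and repeated measures within participants and clusters", and by its wording this covers the feature models. The Social Media Engagement section also names mixed models "to assess changes in engagement over time while accounting for clustering within promotores and neighborhood clusters under the stepped-wedge design", but that sentence concerns change over time, not post features. Neither place mentions a within-promotor comparison.

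The same section later states: "These analyses will provide insight into how different types of communication strategies influence both the extent and quality of interaction". The Background hypothesizes that "narrative-based posts will result in greater engagement and improved decision-making in favor of recommended immunizations". The feature models are the only analysis described that addresses the engagement half of that hypothesis. The Discussion lists as a limitation that "variation in social media platform use and engagement across participants may result in heterogeneous exposure to intervention content".

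**The concern.** Except where the curriculum assigns content, each promotor decides whether a post tells a personal story or cites evidence. Promotores also differ in audience size and responsiveness. A random promotor intercept assumes that a promotor's usual engagement level is unrelated to how often he or she uses the feature. When the two are related, the random-intercept coefficient is a weighted mix of the within-promotor and between-promotor associations, and the between part carries the network. Cluster-robust standard errors leave the coefficient as it was. A predictive model without a promotor term makes no adjustment at all.

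At stake is the reading of a secondary but named question: whether narrative posts draw more engagement because of how they are written or because of who posts them. If the relation runs the other way, with better-connected promotores telling fewer stories, the feature would be underrated instead.

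**Working it through.** The article gives no figure for this analysis, so there is none to reproduce. The check asks how large the distortion is when the true effect is zero.

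**From the article:** at least 35 promotores (Sample Size).

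**Assumed, because not given:** log engagement is normal, with a promotor effect u of SD 1. A promotor uses the feature with probability p.
- Set A: residual SD 1, average p about 0.40, and log-odds of p rising by 0.5 or 1.0 per SD of u (odds multiplied by about 1.6 or 2.7).
- Set B: residual SD 0.8, average p 0.50, log-odds of p with SD 1, and correlation with u of 0.3 or 0.6.

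**Formulas,** with J posts per promotor, q = mean of p(1−p), V = variance of p, C = covariance of p and u, and λ = residual variance / (residual variance + J × promotor variance):
- Pooled bias = C / [mean p × (1 − mean p)]
- Random-intercept bias = λJC / [(J−1)q + λ(JV + q)]
- Within-promotor bias = 0

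For normal u with SD 1, C = slope × q in set A and correlation × q in set B.

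**Worked case** (set A, slope 0.5, J = 6): q = 0.2274, V = 0.0130, C = 0.5 × 0.2274 = 0.1137, λ = 1/7 = 0.143.
- Random intercept: numerator 0.143 × 6 × 0.1137 = 0.0975; denominator 5 × 0.2274 + 0.143 × (6 × 0.0130 + 0.2274) = 1.181. Bias = 0.083, ratio 1.09.
- Pooled: 0.1137 / (0.402 × 0.598) = 0.473, ratio 1.60.

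**Spurious engagement ratio when the true ratio is 1.00:** closed form, with the simulated value in parentheses (400 runs per setting for A, 600 for B).

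| Model | A, slope 0.5 | A, slope 1.0 | B, corr. 0.3 | B, corr. 0.6 |
|---|---|---|---|---|
| Random intercept, 3 posts | 1.18 | 1.37 | 1.07 (1.07) | 1.15 (1.16) |
| Random intercept, 6 posts | 1.09 (1.09) | 1.17 (1.18) | 1.03 (1.04) | 1.07 (1.06) |
| Random intercept, 12 posts | 1.04 (1.05) | 1.09 (1.09) | 1.02 (1.01) | 1.03 (1.03) |
| Random intercept, 24 posts | 1.02 (1.02) | 1.04 (1.05) | 1.01 (1.01) | 1.02 (1.01) |
| No promotor term | 1.60 (1.60) | 2.29 (2.30) | 1.28 (1.27–1.28) | 1.64 (1.60–1.65) |

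**False-positive rates in simulation, nominal 5%:**
- Random intercept, set A: 8–18% at 6 posts, 9–11% at 12, 7–11% at 24.
- Random intercept, set B: 6–11% over 3 to 24 posts.
- Pooled with cluster-robust errors, set B: 16–30% at correlation 0.3 and 47–88% at 0.6.
- Within-promotor, set B: 4–7%, with estimated ratios of 0.99–1.01.

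**Limiting case:** if every promotor posts the same mix, V and C are zero and every method gives 1.00.

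**Price of the within-promotor estimate:** the standard error grows by √(random-intercept denominator / [(J−1)q]). In the worked case this is √(1.181/1.137) = 1.02. Over both sets it is 1.02–1.03 at 6 posts and 1.07–1.10 at 3.

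**The case against.** The strongest reply is that the article does not fix the parameterization. It does not rule out fixed effects, centring or grouped folds, and such details commonly sit in a full protocol or SAP that is not shown. The general rule in Data Analysis also reaches the feature models. This stands in part. A reader might infer that the plan will ignore promotor altogether and so expect ratios of 1.6–2.3. The text does not support that, because the general rule requires repeated measures to be accounted for. Those larger figures apply only if the rule is met by robust errors alone, or if the machine-learning models carry no promotor term.

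A second reply is that the residual bias under a random intercept is modest and fades with more posts. This also stands. The standardized and final posts assigned in sessions 5 and 6 of Table 1 number only about three, but monthly payment for campaign posting (Participants) implies more, in an unstated number.

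A third reply is that Table 1 assigns every promotor both standardized informational posts and an own infographic whose drafted caption includes a narrative. For those posts the mix is nearly common and the bias nearly vanishes. That is correct, and it supplies the comparison that the feature models should use. It does not cover the freely chosen campaign posts.

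Finally, the stated aim is association, and the sentence on influence follows a plan to study audience responses. A reader might infer that the article commits to a causal reading of every feature, or that popular promotores' habits are bound to be mistaken for good messages. Neither is fixed by the text, and the second also needs popularity and style to be correlated. What remains is that the Background hypothesis is causal in form, while the stated adjustment corrects dependence without separating promotor from message.

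**Conclusion.** The point holds as a weakness of method in a non-primary analysis. Accounting for clustering does not separate within-promotor from between-promotor association, so a feature may take some credit that belongs to the network. Under the assumed inputs the spurious ratio with a random promotor intercept is about 1.04–1.18 at 6 posts each and 1.01–1.05 at 24. It is about 1.3–2.3 where promotor is absent from the mean model, and 1.00 where all promotores share the same feature mix. The spread of engagement, the number of posts and the link between popularity and style are all assumptions, as is the use of a linear model on log engagement in place of the planned count models. The primary outcome, decision-making among network members, is not affected.

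**What to change.** In the feature models, use promotor fixed effects, or enter each feature as the promotor's mean plus the post's deviation from it, and report the within-promotor coefficient as the result. For the narrative hypothesis, use the Table 1 contrast of standardized informational posts against the promotor's own narrative posts. Note that authorship and order change together with narrative in that contrast. In the predictive models, use the same centred features and group the validation folds by promotor, so that a model earns no credit for recognizing who posted.

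This removes only stable differences between promotores. Topic, timing and platform can still differ from post to post, so the wording on how strategies influence interaction should become associational wherever such confounding remains.

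The cost is a sentence or two in the analysis section and no new data. Promotores who always or never use a feature add nothing to its within-promotor estimate, so intervals widen: by about 2–3% at 6 posts each and 7–10% at 3 under the assumptions above, and by more if use of a feature is nearly all-or-none.
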